### Self-reference effect task in virtual reality

Virtual reality immersion will be achieved using the HTC VIVE Pro Eye (Taoyuan City, Taiwan: HTC corporation) virtual reality headset. The self-reference effect task will consist in a walk through a virtual city, where participants will encounter a total of 32 multisensory daily life events that aim to be incidentally encoded in episodic memory. Participants will embody a virtual avatar and navigate twice through two distinct parts of the city. Prior to each navigation, avatar embodiment will be induced using a visuomotor stimulation in front of a virtual mirror, asking participants to move their different body parts while looking at them directly or in the mirror. To manipulate the minimal self-reference, one navigation will be associated with a synchronous avatar to induce a high sense of embodiment, and therefore a stronger sense of minimal self. The other navigation will be associated with an asynchronous avatar with a 700 ms-delay between participants’ real performed movements and the seen movements of the avatar, to induce a low sense of embodiment, and thus a weaker sense of minimal self. To manipulate the narrative self-reference, in each navigation path, half of the events will be associated to the participants themselves (Self), and the other to someone else (Other). The association will be induced by asking participants to take a picture of each event and rate its personal significance for either Self or Other. All conditions will be counterbalanced.

Following each navigation, participants will be submitted to self-reported questionnaires assessing their sense of embodiment (Embodiment Questionnaire) [85], sense of presence (Igroup Presence Questionnaire) [86], cybersickness (Simulator Sickness Questionnaire) [87], and current emotional state (Mood Visual Analogue Scale) [88].

Finally, participants will undergo two episodic memory tests: a free recall task and a recognition task. The free recall will be based on a verbal interview of 20 min, during which participants will be asked to recall all the events that they remember encountering in the virtual city. The recognition test will be programmed using the Python module Neuropsydia [89] and consists of displaying on a computer screen all 32 encountered events mixed with 16 lures which were not encountered in a random order, and asking participants whether they encountered this event in the virtual city. For both memory tests, participants will be asked to provide systematically and the most precisely possible, for each recalled event: description of the event, spatiotemporal situation, source, referent for the personal significance rating, perceptive and phenomenological details, degree of reliving or familiarity of the event. This task has been designed by [name] under the supervision of [name], and derived from [name]’s protocol for the procedures linked to the minimal self-reference [90]. The virtual environment has been developed by [name] using Unity.

### Polysomnography

An overnight polysomnography with 19 EEG channels and ventilatory polygraphy will be recorded for all participants within the first two months of inclusion, at the sleep medicine department of Hôtel-Dieu hospital, in Paris (Centre du Sommeil et de la Vigilance). Trained sleep technicians will set-up the head-sets in the evening and supervise the recording during the night. The recordings will be analyzed by trained sleep specialists (SR, LD).

### Microstates analysis

Microstate analysis will be performed on eyes-closed resting-state, during the sensorimotor integration task, and during sleep. A minimal preprocessing will be done with the MNE EEG software on Python, which includes a bandpass filter between 0.5 and 40 Hz, rereferencing to the mean, and visual and automatic correction for artifacts using independent component analysis (ICA). Each recording will be visually reanalyzed by clinical neurophysiologists to check for any residual artifact. Microstate analysis will be done using the Pycrostates package [91]. Global field power (GFP) will be determined for each participant. Only EEG topographies at GFP peaks will be retained to determine microstates’ topographies, through a modified K-means clustering. For each subject the same number of GFP peaks will be extracted and concatenated into a single data set for clustering. A combined score will be used to compute the optimal number of clusters. The resulting clusters will be backfitted to each individual maps. Temporal smoothing will be used to ensure that periods of inter-peak noise, of low GFP, did not interrupt the sequences of quasi-stable segments. For each subject, three parameters will be computed for each microstate class: frequency of occurrence (“occurrence”), temporal coverage (“coverage”) and mean duration. Occurrence is the average number of times a given microstate occurs per second. Coverage (in %) is the percentage of total analysis time spent in a given microstate. Mean duration (in ms) is the average time during which a given microstate was present in an uninterrupted manner (after temporal smoothing).

### Biological sampling

Peripheral blood samples will be collected for genetic, epigenetic, proteomic, and metabolomic studies.

### Statistical power estimates

We considered a minimum expected effect size around 0.5, based on pairwise comparisons of EEG microstate parameters (mean duration, time coverage, occurrence) between chronic schizophrenia and relatives of subjects with schizophrenia [14]. Accepting an alpha risk of 0.05 and 95% power, we estimate the necessary number of subjects to be included in each of the 6 groups at 15 (calculated in R with the pwr.anova.test function) (Fig. 2). Given the risk of overestimating the minimum effect size associated with publications based on small cohorts, we estimate that a number of 21 subjects significantly increases the chances of obtaining a power greater than 95%. This represents a total of 126 subjects.

**Fig. 2 Fig2:**
[figure not shown]
Power calculation

### Statistical analysis design

For all neurophysiological variables, the investigators will apply a repeated measures ANOVA, and use the following contrasts:“UHR, FEP, SCZ, ASD, MDD” vs. “Healthy subjects”, in order to test the variables as markers of general psychopathology;“UHR, FEP, SCZ” vs. “ASD, MDD”, in order to test the variables as specific markers of psychosis; equivalently, their specificity in MDD and ASD will be tested);“UHR” vs. “FEP" vs. “SCZ”, in order to test the variables as markers of state;Finally, in a dimensional approach, the functional correlates of microstates will be studied across wakefulness and sleep, and during speech, regardless of diagnosis.

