## Abstract

**Background:**

Quantitative electroencephalography (EEG) analysis offers the opportunity to study high-level cognitive processes across psychiatric disorders. In particular, EEG microstates translate the temporal dynamics of neuronal networks throughout the brain. Their alteration may reflect transdiagnostic anomalies in neurophysiological functions that are impaired in mood, psychosis, and autism spectrum disorders, such as sensorimotor integration, speech, sleep, and sense of self. The main questions this study aims to answer are as follows: 1) Are EEG microstate anomalies associated with clinical and functional prognosis, both in resting conditions and during sleep, across psychiatric disorders? 2) Are EEG microstate anomalies associated with differences in sensorimotor integration, speech, sense of self, and sleep? 3) Can the dynamic of EEG microstates be modulated by a non-drug intervention such as light hypnosis?

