**Methods:**

This prospective cohort will include a population of adolescents and young adults, aged 15 to 30 years old, with ultra-high-risk of psychosis (UHR), first-episode psychosis (FEP), schizophrenia (SCZ), autism spectrum disorder (ASD), and major depressive disorder (MDD), as well as healthy controls (CTRL) (*N* = 21 × 6), who will be assessed at baseline and after one year of follow-up. Participants will undergo deep phenotyping based on psychopathology, neuropsychological assessments, 64-channel EEG recordings, and biological sampling at the two timepoints. At baseline, the EEG recording will also be coupled to a sensorimotor task and a recording of the characteristics of their speech (prosody and turn-taking), a one-night polysomnography, a self-reference effect task in virtual reality (only in UHR, FEP, and CTRL). An interventional ancillary study will involve only healthy controls, in order to assess whether light hypnosis can modify the EEG microstate architecture in a direction opposite to what is seen in disease.

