### Objectives of the DEMETER study

Building on our preliminary results, the DEMETER project (“Détermination Des Microétats EEG associés Aux Troubles Psychiques Dans Les États à Risque”—EEG Microstates Across At-Risk Mental States) is a prospective observational study that aims to characterize the EEG microstate signature with regard to underlying neurophysiological functions, including sensorimotor integration, speech, sleep, and sense of self, across a population of adolescents and young adults, with ultra-high-risk of psychosis (UHR), first-episode psychosis (FEP), schizophrenia (SCZ), autism spectrum disorder (ASD), and major depressive disorder (MDD), compared with healthy controls (CTRL) (*N* = 21 × 6), between two timepoints one year apart.

Participants will undergo deep phenotyping based on psychopathology and neuropsychological assessments at baseline and after one year of follow-up, high-resolution EEG (64 electrodes) with a resting period and a sensorimotor task, a recording of the characteristics of their speech (prosody and turn-taking), a one-night polysomnography, and biological sampling for multi-omic analyses, and a self-reference effect task in virtual reality (the latter only in UHR, FEP, and CTRL).

The main questions it aims to answer are as follows. 1) Are EEG microstate anomalies associated with specific disorders, and clinical and functional prognosis, both in resting conditions and during sleep ? 2) Are EEG microstate anomalies associated with differences in sensorimotor integration, speech, and sense of self ? 3) An interventional ancillary study will involve only healthy controls, in order to assess whether light hypnosis conditions can modify the EEG microstate architecture in a direction opposite to what is seen in disease.

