## Methods

### Participant recruitment

All participants will be included at the Clinical Research Centre (CRC), University Hospital Group Paris Psychiatry and Neurosciences (GHU). Inclusion criteria are: an age between 15 and 30 years old; French as the maternal language or spoken in the context of bilingualism; a DSM-5 diagnosis of schizophrenia or major depressive disorder or autism spectrum disorder; a diagnosis of ultra-high-risk of psychosis or first-episode psychosis based on the Comprehensive Assessment of at risk mental state (CAARMS) translated in its French version [77]; and healthy control subjects recruited from the general population. Exclusion criteria are: suicidal risk; severe or non-stabilized somatic and neurological disorders; epilepsy; head trauma; IQ below 70; presence of other psychiatric disorders (bipolar disorder, obsessive–compulsive disorder, or substance use disorders, except for tobacco or cannabis, tolerated up to 5 joints/day); for healthy control subjects, a family history of psychosis is an exclusion criterion. Pregnant or breast-feeding women will not be included.

Participants will be screened among the population of patients seen at an early psychosis outpatient clinic (Centre d’évaluation des jeunes adultes et adolescents—CJAAD, GHU). Healthy controls will be reached through the healthy volunteers database of the CRC. Participant assessment will be as follows (Fig. 1, Table 1). 1) During the pre-inclusion visit, participants will be informed of all the details of the protocol, orally and in writing, and eligibility criteria will be verified. Then a two-week reflection period will be observed, before the signature of a written consent at the baseline inclusion. 2) The baseline visit will consist of a first visit of three half-day sessions including medical, psychopathological and neuropsychological assessments, biological sampling (described below), and speech recording. In the following two months, participants will undergo one night of polysomnography (everyone) and two half-day sessions for the sensorimotor task (everyone) followed by light hypnosis (only controls), and the self-reference effect task in virtual reality (only controls, UHR, and FEP). 3) The follow-up visit will consist of a second psychopathological and neuropsychological assessment, biological sampling, and shorter EEG recording (5–10 min).

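### One repeated-measures ANOVA is prescribed for every neurophysiological variable: with visit as the factor it can drop participants lacking a second EEG, it does not suit single-value baseline measures, and no listed analysis addresses prognosis

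*Protocol article*

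**What the plan says.** The section on statistical analysis design names one model: "For all neurophysiological variables, the investigators will apply a repeated measures ANOVA, and use the following contrasts". Three sets of contrasts follow: all patient groups against controls, the psychosis-spectrum groups against ASD and MDD, and UHR, FEP and SCZ against one another. A further sentence adds that "in a dimensional approach, the functional correlates of microstates will be studied across wakefulness and sleep, and during speech, regardless of diagnosis", without naming a model.

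The Objectives describe groups compared "between two timepoints one year apart". Under Participant recruitment, "The follow-up visit will consist of a second psychopathological and neuropsychological assessment, biological sampling, and shorter EEG recording". Other recordings are made once. The Abstract (Methods) says "At baseline, the EEG recording will also be coupled to a sensorimotor task and a recording of the characteristics of their speech", and lists polysomnography and the virtual-reality task at the same timepoint. The Polysomnography section says the overnight recording "will be recorded for all participants within the first two months of inclusion".

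The Abstract's first question is: "Are EEG microstate anomalies associated with clinical and functional prognosis, both in resting conditions and during sleep, across psychiatric disorders". The Objectives put it more broadly: "Are EEG microstate anomalies associated with specific disorders, and clinical and functional prognosis, both in resting conditions and during sleep". The Discussion again gives prognosis as an aim.

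**The concern.** A repeated-measures ANOVA needs a within-person factor, and in its classical form it needs every level of that factor for every person analysed. The article prescribes the model across the board without naming the factor. Three things follow.

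- **Resting EEG.** If visit is the factor, a participant lost before one year leaves the analysis entirely, and a valid baseline recording is thrown away with them.
- **Measures taken once.** A whole-night sleep summary or a per-person speech summary has no second visit and no obvious within-session condition, so the prescribed model has nothing to repeat over.
- **Prognosis.** Comparing diagnoses does not show whether a baseline microstate parameter predicts later symptoms or functioning. The outcome data will be collected, but no listed analysis uses them for this purpose.

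At stake are precision and possible selection bias in the group comparisons, and a stated aim that the plan, followed literally, would not answer. If the prognostic analysis is chosen later, there is wide freedom of choice: each microstate class has three parameters and there are several clinical scales.

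**Working it through.** **1. The plan's own sample size.** Inputs from Statistical power estimates: 6 groups, effect size 0.5 (Cohen's f in the R function cited), alpha 0.05, power 95%. For a one-way ANOVA the noncentrality is 6 × n × f², with 5 and 6(n − 1) degrees of freedom.

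- n = 14: noncentrality 21.0, power 94.8%
- n = 15: noncentrality 22.5, power 96.2%
- n = 21: noncentrality 31.5, power 99.6%

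The stated 15 per group is reproduced. The increase to 21 is justified by a possibly overestimated effect size, not by attrition; no loss rate is given. The calculation covers one measurement per person, so it addresses neither the repeated-measures model nor prognosis.

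**2. Loss under a visit-factor ANOVA.** The loss rates are assumptions.

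- Completers per group: 21 × 0.85 = 17.9 at 15% loss; 21 × 0.70 = 14.7 at 30%.
- Standard error of a baseline contrast, relative to using all 21: 1/√(1 − loss) = 1/√0.85 = 1.08 and 1/√0.70 = 1.20.

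One-way ANOVA power, with completers rounded down:

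| Loss | n per group | f = 0.5 | f = 0.4 |
|---|---|---|---|
| 0% | 21 | 99.6% | 94.4% |
| 10% | 18 | 98.7% | 89.8% |
| 20% | 16 | 97.3% | 85.2% |
| 30% | 14 | 94.8% | 78.9% |

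These use the plan's one-measurement formula as an approximation to the group comparison.

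**3. Which variables have a repeated factor.**

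- Resting EEG: visit (baseline, one year). The follow-up EEG is only described as shorter; that it is a resting recording is inferred.
- Sensorimotor task: blocks at different congruency levels, within session.
- Virtual-reality task: avatar synchrony and Self/Other, within person.
- Microstates: several classes per recording, and wakefulness versus sleep.
- Whole-night sleep summaries and per-person speech summaries: none evident.

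**4. Prognosis.** All three sets of contrasts have diagnosis as the explanatory variable. The dimensional sentence concerns wakefulness, sleep and speech, and mentions no one-year outcome. So nothing listed relates a baseline microstate parameter to one-year SOFAS, PANSS, MADRS or CAARMS.

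**5. Could prognosis be tested with the planned data?** Patients: 5 × 21 = 105; with an assumed 25% loss, 105 × 0.75 ≈ 79. For a partial correlation r with c covariate terms, power ≈ Φ(atanh(r) × √(n − c − 3) − 1.96). Baseline outcome (1 term) and diagnosis (4 terms) give c = 5; adding, say, age and sex gives c = 7. Take atanh(0.25) = 0.2554 and atanh(0.30) = 0.3095.

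- n = 105, c = 7: √95 = 9.747; 0.2554 × 9.747 − 1.96 = 0.53, power 70%; 0.3095 × 9.747 − 1.96 = 1.06, power 85%. With c = 5: 71% and 86%.
- n = 79, c = 7: √69 = 8.307; 0.2554 × 8.307 − 1.96 = 0.16, power 56%; 0.3095 × 8.307 − 1.96 = 0.61, power 73%. With c = 5: 58% and 74%.

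These are for one two-sided test at 0.05 with no multiplicity adjustment. The values of r are assumptions.

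**The case against.** The best defence is that the article never says visit is the repeated factor. Task blocks, virtual-reality conditions and microstate classes are proper within-person factors, and repeated-measures ANOVA is ordinary for them. This stands. A reader might infer that the model is wrong for everything recorded only at baseline; the task descriptions do not support that, and the misfit is confined to measures with one value per person.

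A reader might also infer that the plan definitely discards non-completers and that its estimates are biased. Neither is shown. The first needs visit as the factor and a complete-case implementation. On the second, loss that depends only on diagnostic group, which is in the model, leaves complete-case group means unbiased. Bias needs loss related to the outcome within groups, and the article gives no attrition data.

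As to power, 21 per group leaves room: 30% loss brings the groups back to about the 15 required. That is fair at 0.5, but the margin was set aside for a smaller effect and cannot serve both purposes in full.

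A further tempting reading is that question 1 goes wholly untested. In the Objectives it includes association with specific disorders, which the contrasts do test. Only the prognosis part lacks an analysis, though in the Abstract that part is the whole question.

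Finally, this is a condensed article, and a fuller plan may settle missing data and the prognostic model. Their absence alone would be no finding. The point rests on what the article does fix: one model for all variables, with a listed set of analyses that does not match a stated aim.

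**Conclusion.** The point holds in a limited form. The firmest part is prognosis: it is a stated aim, the one-year assessments will exist, and no listed analysis uses them to test it. Next, the blanket prescription gives no workable model for single-value baseline measures. Third, and conditional on a classical ANOVA with visit as the factor, resting-EEG comparisons lose everyone without a second recording. That makes baseline standard errors 8–20% larger at an assumed 15–30% loss and opens a possibility, not a demonstrated fact, of selection bias. Omnibus power is little affected at the planned effect size (about 95% at 30% loss) but drops from 94% to 79% at 0.4. This is worth correcting before analysis; it does not undermine the design.

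**What to change.** Replace the single prescription with one line per type of variable, keeping the planned diagnosis contrasts:

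- **Resting EEG:** a linear mixed model with group, visit, group × visit and a random participant effect, using all available recordings. It keeps baseline data from non-completers and allows loss to depend on group and on the observed recording.
- **Baseline-only measures with within-session conditions** (task blocks, virtual-reality conditions, microstate classes): a repeated-measures or mixed model with condition as the named within-person factor. A purely between-group model would remove the within-person effects that the hypotheses concern.
- **Single-value baseline measures:** a between-group model.
- **Prognosis, in patients:** regress one pre-named one-year outcome (SOFAS, for example) on one pre-named baseline resting microstate parameter, adjusting for the baseline value of the outcome and for diagnosis; repeat for sleep microstates. Other parameters and scales should be labelled secondary or exploratory, since the power above is for one test and is modest if a quarter of patients are lost.

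The cost is revised analysis wording and a few more model fits. No new data or visits are needed.

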This protocol describes a transdiagnostic longitudinal case–control study that includes a multimodal neurophysiological assessment of sensorimotor integration, speech, sleep, and sense of self, in patients with major depressive disorder, ultra-high-risk of psychosis, first-episode psychosis, schizophrenia, and autism spectrum disorders, compared to healthy controls, in a population of adolescents and young adults aged 15 to 30 years old. Preliminary retrospective analyses from our group, with routine clinical low-resolution EEG recordings, have suggested that a variation in EEG microstates class D may be a marker of stage across psychotic disorders, as it decreases from UHR to FEP and schizophrenia. However, these changes were not specific to psychosis, and they appeared to reflect a shared dimension on the schizophrenia-autism spectrum. We also suggested that a microstate ratio imbalance between class C and class D may perhaps be more specific to schizophrenia, although it did not appear that EEG microstates were sufficient to differentiate between different groups of diseases [18]. Building on this preliminary data, we propose this prospective study with higher resolution EEG recordings to test whether anomalies in the EEG microstate architecture may be associated with diagnosis, clinical and functional prognosis, both in resting conditions and during sleep, across psychiatric disorders. We postulate that we may find EEG microstate anomalies associated with differences in sensorimotor integration, speech, sense of self, and sleep, and that the dynamic of EEG microstates may be modulated by a non-drug intervention such as light hypnosis, as a proof-of-concept of potential usefulness in psychotherapeutic approaches.

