We further hypothesize that the attentional component of somatosensory integration in preparation for a motor response is modulated through visuo-tactile stimuli in healthy subjects, and is altered in patients with psychotic disorders, probably with abnormal inhibition mechanism responses. Specifically, we expect that primary sensory cortex activity, measured as alpha and beta oscillations, influences motor cortex excitability and would be desynchronized in psychosis. We also anticipate an impaired connectivity among the primary sensorimotor network, as well as altered synchrony states in an attentional context. Finally, at rest, we expect these anomalies to be associated with a C/D microstate imbalance and with microstate class E anomalies (postulated to be correlated with interoception and sensorimotor processing).

We also expect to find differences in prosodic and turn-taking patterns between patients and healthy controls. In particular, we predict all patients to display reduced pitch variability, reduced speech output and increased pause duration. Moreover, we expect patients’ voices to overlap more with the interlocutor’s. We also hypothesize that linguistic cues could be markers of the stage, with increasing levels of atypicality from UHR to SCZ. Finally, we speculate that patients with ASD and participants along the schizophrenia spectrum will present similar prosodic and turn-taking patterns.

FInally, we postulate a reduced self-reference effect on memory performance in UHR and FEP individuals, due to patients’ self disturbances. Specifically, we expect a preserved narrative self-reference effect but no minimal self-reference effect in UHR and FEP individuals, since minimal self disturbances are already present in early stages of psychosis whereas narrative disturbances of the self are less marked, as opposed to controls who are expected to exhibit both minimal and narrative self-reference effects.

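### The contrast read as psychosis specificity compares psychosis only with the average of ASD and MDD, so it can be significant when ASD shares the anomaly

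*Protocol article*

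**What the plan says.** The section Statistical analysis design of the protocol article applies a repeated measures ANOVA to all neurophysiological variables and names three contrasts, each with its purpose.

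- Contrast 1: "UHR, FEP, SCZ, ASD, MDD” vs. “Healthy subjects”, in order to test the variables as markers of general psychopathology".
- Contrast 2: "UHR, FEP, SCZ” vs. “ASD, MDD”, in order to test the variables as specific markers of psychosis". A parenthesis adds that "equivalently, their specificity in MDD and ASD will be tested", without writing out a contrast.
- Contrast 3 compares UHR, FEP and SCZ with one another, as markers of state.

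Controls appear only in contrast 1, where all five patient groups are pooled against them.

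Two statements in the Discussion bear on contrast 2. On the preliminary class D finding, the article reports that "these changes were not specific to psychosis, and they appeared to reflect a shared dimension on the schizophrenia-autism spectrum". On speech, it expects that "patients with ASD and participants along the schizophrenia spectrum will present similar prosodic and turn-taking patterns".

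**The concern.** A marker is specific to psychosis if the psychosis groups depart from normal and the other patient groups do not depart in the same way. Contrast 2 is given that purpose, but its null hypothesis is only that the psychosis mean equals the average of the ASD and MDD means. That null can be false while specificity is also false:

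- **Case (a):** ASD has the same anomaly as psychosis and MDD has less or none. Averaging ASD with MDD then leaves a gap.
- **Case (b):** the psychosis groups equal controls, and ASD, MDD or both are abnormal. Controls have weight zero, so contrast 2 taken alone cannot see this.

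Case (a) matters more, because the preliminary class D result points to sharing between schizophrenia and autism. At stake is whether a marker shared by autism and psychosis could be reported as particular to psychosis.

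**Working it through.** **Inputs.** There are 6 groups of 21 and alpha is 0.05 (section Statistical power estimates). The article gives no effect size for a contrast, so 0.5/0.8/1.0 SD is an assumed range. Also assumed are equal weights within each set of groups, equal SDs of 1, one measurement per subject and two-sided tests. The repeated-measures correlation is not given and was not modelled.

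**The plan's own figure.** A one-way ANOVA with 6 groups, effect size 0.5 entered as Cohen's f, and alpha 0.05 gives power 94.8% at 14 per group and 96.2% at 15. The stated 15 is reproduced. At 21 per group power is 99.6%. That figure concerns the overall F test and says nothing about what contrast 2 identifies.

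**Contrast 2.** Weights are 1/3 for UHR, FEP and SCZ, −1/2 for ASD and MDD, and 0 for controls.

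- Standard error = √[(3 × 1/9 + 2 × 1/4)/21] = √(0.8333/21) = 0.199 SD.
- Degrees of freedom = 6 × 20 = 120. Rejection rates come from the non-central t distribution.

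Expected value when psychosis and ASD are both shifted by d:

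- MDD normal: d − (d + 0)/2 = d/2. At d = 0.8 this is 0.40, and 0.40/0.199 = 2.01.
- MDD at half: d − (d + d/2)/2 = d/4.
- MDD at d: d − (d + d)/2 = 0.

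Probability that contrast 2 is significant:

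| True pattern | 0.5 SD | 0.8 SD | 1.0 SD |
|---|---|---|---|
| (a) ASD shares fully, MDD normal | 24% | 51% | 70% |
| ASD shares fully, MDD has half | 10% | 17% | 24% |
| ASD and MDD both share fully | 5% | 5% | 5% |
| (b) Psychosis normal, ASD and MDD abnormal | 70% | 98% | 99.9% |
| (b) Psychosis normal, only MDD abnormal | 24% | 51% | 70% |
| Truly psychosis-specific | 70% | 98% | 99.9% |

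On contrast 2 alone, the fourth and last rows cannot be told apart.

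**Contrasts 1 and 2 read together.** Requiring both to be significant in the same direction (simulation, 200,000 replicates) gives:

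- Case (a), MDD normal: 9%/39%/64%.
- Case (b): about 0.2% or less. When psychosis is normal, the two contrasts have opposite signs. At d = 0.8 with ASD and MDD both lowered, contrast 1 expects −0.32 and contrast 2 expects +0.80.
- Truly specific effect: 17%/50%/70%.

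The joint reading therefore largely removes case (b) but leaves case (a).

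**The parenthesis.** Suppose it means ASD, and separately MDD, each against the other four patient groups. In case (a) with MDD normal, the ASD contrast is d − (3d + 0)/4 = d/4, significant in 8%/13%/17%. The MDD contrast is 0 − d = −d, significant in 53%/90%/98%.

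**Separate comparisons.** Suppose psychosis must differ in the same direction from controls, from ASD and from MDD, each at two-sided 0.05 (simulation, 200,000 replicates). False labels are then 1.4%/2.3%/2.5% in case (a) with MDD normal, the same when psychosis is normal and both ASD and MDD are abnormal, and about 0.2% when only MDD is abnormal. Power for a truly specific effect is 19%/72%/93%.

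**The case against.** The strongest reply is that the article never says a significant contrast 2 is enough to declare specificity. Its contrasts apply together to every variable, and the direction of effect and the group means will be visible. This stands for case (b): the 70%/98%/99.9% describes contrast 2 in isolation, and contrast 1 with the direction of effect would largely expose the error. It does not dispose of case (a), where 9%/39%/64% remain.

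Second, the parenthesis about MDD and ASD, read as each against the other patients, covers the ASD-versus-MDD difference that the three written contrasts leave out, and it would usually flag MDD as the outlier. That is a fair reading. But those contrasts are not written out, nothing ties the psychosis label to them, and they include no controls.

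Third, a reader might infer that the team expects exactly the pattern that misleads contrast 2. The article does not support that. It nowhere says MDD is normal: the Background cites microstate disruption in depression, and the Discussion predicts several speech changes in every patient group, MDD included. The more MDD shares the anomaly, the smaller the error, down to the nominal 5%. The team also describes its own class D finding as not specific, so it is alert to the distinction.

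Finally, follow-up pairwise comparisons may sit in an analysis plan that is not shown. That is why the point is confined to the contrast and the purpose that the article itself states.

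**Conclusion.** The point holds with moderate severity. Contrast 2 tests psychosis against the average of ASD and MDD, which is not what its stated purpose requires. The consequential error is sharing with ASD: a significant result in 24%/51%/70% of trials if MDD is normal, falling to 10%/17%/24% if MDD has half the anomaly and 5% if it shares it fully. In the first case, adding contrast 1 in the same direction leaves 9%/39%/64%. Sharing with ASD is plausible from the article's preliminary data. The state of MDD is not given, so no single rate in this range can be called the expected one.

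The figures rest on the assumed effects and on the simplifications listed above. The structural statement, that contrast 2 expects d/2 when ASD shares fully and MDD is normal, depends only on equal weighting. It would be too strong to say that the plan will publish shared markers as psychosis-specific, or that the study cannot answer the question: all six groups are recruited and every comparison remains available.

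**What to change.** In Statistical analysis design:

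1. Relabel contrast 2 as psychosis versus the average of the other patient groups.
2. Add psychosis versus ASD, psychosis versus MDD, psychosis versus controls, and ASD versus MDD, each with a confidence interval.
3. Write out the contrasts meant by the remark on MDD and ASD.
4. Call a variable psychosis-specific only when psychosis departs in the same direction from ASD, from MDD and from controls.

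Requiring each of the three comparisons in item 4 at 0.05 is one option. Because all three must succeed, it needs no further multiplicity adjustment, and false labels in the cases above fall to about 0.2–2.5%. The price is power for a truly specific effect of 19%/72%/93%, against 70%/98%/99.9% for contrast 2 alone, so a specific effect of 0.5 SD would usually be missed as a formal claim. If that is too strict, the separate estimates and intervals can be reported without a formal gate, with the wording of any specificity claim limited accordingly.

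The change affects analysis text only. Recruitment, measurements and sample size stay as they are.
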